**3.9.2 Propensity score matching**

Propensity score matching is proposed to identify people that will be comparable to the cohort participants. By definition, a propensity score is the probability of treatment assignment conditional on observed baseline covariates. Therefore, among people with the same propensity score, the distribution of observed baseline covariates will be the same between treated and untreated groups. An estimated propensity score can be obtained by regressing treatment status on observed baseline covariates. To reduce observed confounding participants can be matched based on the propensity score. Estimated treatment effects can then be obtained by directly comparing outcomes between matched groups using appropriate methods for matched samples. Propensity score matching mimics some aspects of randomization of a traditional trial but uses observational data. However, unlike a randomized trial, propensity score matching can only account for measurable confounding and not unmeasurable confounding.

For the purpose of this study a propensity score will be calculated based on all covariates that can impact treatment assignment and outcomes. Linked cohort participants will be matched to people in the health administrative data based on 1:1:1 ratio, without replacement, on the propensity score to ascertain two additional exposure groups. This will enable the comparison of three exposures (CAMH services, community services, eligible but no service).

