**3.9.1 Study population and design**

Participants who consent to have their data linked with administrative health data will be eligible to have both historical and future services use linked from the time of cohort entry. Participants who have a OHIP card will be able to consent for direct linkage, and participants who consent but have any uncertainty with their OHIP number will be linked using a deterministic process.

Further use of administrative data will enable comparison of service use and outcome between:

1. Participants that are part of the cohort at CAMH (accessing specialized mental health services at CAMH),
2. People with a SSD who are accessing specialized mental health services in the community (including ACT, ICM and case management services but not at CAMH), and
3. People with a SSD who reside in Toronto but are not currently receiving specialized mental health services

Diagnosis of a SSD in the comparison groups in the health administrative data will be ascertained using a validated algorithm that captures all incident cases of SSD [(Kurdyak et al., 2015)](https://www.zotero.org/google-docs/?SkNgwy). The comparison groups will be restricted to people who reside in areas of Toronto where outpatient services at CAMH are offered and restricted to people who have not received regular outpatient services at CAMH.

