**3.9.5 Covariates**

Covariates that will be accounted for will include: age, sex, immigration status, neighbourhood-level marginalization (consider neighbourhood as well), diagnosis, history of substance use related health care contacts, enrollment with a family physician, ODB eligibility, long-acting antipsychotic medication claims, claims for medications for specific comorbid health issues (i.e., metformin, statins), regular metabolic monitoring, regular CBC monitoring for clozapine use (as at the present time clozapine claims are not regularly reported).

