Recruitment of participants for this study will take place across all outpatient and inpatient clinical services at CAMH where individuals with SSDs may be receiving care, and include both new and existing patients receiving clinical services. Sequential cohorts of participants will be recruited based on duration of illness, enabling an accelerated longitudinal design for this study that will serve to maximize coverage of longitudinal functional trajectories across illness stages. Through regular monitoring of participant recruitment, we will balance recruitment across these multiple cohorts. Core research assessments will mirror measurement-based care assessments and metabolic monitoring being implemented across these clinical services, with sharing of assessment results with the patient’s clinical team. All participants will be offered the opportunity to participate in the neuroimaging and additional laboratory/biological components of this study either as part of this study, or ideally through shared participation in existing complementary studies already taking place in the Division. Harmonization of study assessments and data sharing with existing clinical research studies will enable integration and collaboration across clinical research studies in the Division, maximize recruitment efforts, and leverage existing funded research studies for data collection. With regards to the potential participant pool from which individuals could be recruited, current patient volumes across Schizophrenia Division outpatient clinical services at CAMH, for example, indicate that over 4000 unique patients were seen over the past year, with an average of over 1900 patients seen per month. Based on these volumes, and the integration of study assessments for this proposed work within the context of routine clinical care for such patients within existing clinical services at CAMH, this study will aim to recruit 500 participants per year for 2 years, yielding a total sample of 1000 participants enrolled in this study (i.e., approximately 10 participants per week from over 15 outpatient and inpatient clinical services).

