**8.0 IMPACT AND INNOVATION**

At a population and health systems level, our work has the potential to identify and predict individual recovery and functional trajectories at the individual patient level, and develop and study real-world interventions to improve functional outcomes, recovery, and community functioning. This is predicted to enhance the precision and effectiveness of interventions to address disability for people with SSDs, support the development of more cost-effective service designs, and reduce the economic costs associated with SSDs.

From a neuroscience and biological perspective, we will be able to identify biological and metabolic profiles, physical health parameters, and structural and functional properties of brain circuits that are associated with, and which may predict different illness and functional trajectories.

We foresee that this work will create a very unique, multidisciplinary training platform which will attract the best and brightest trainees from diverse backgrounds. Principles of data sharing and multi-level data-driven techniques will build a spirit of collaboration and altruism across the Centre. By training the nex47t generation of investigators, we will increase the number of highly qualified personnel committed to improving the mental health of individuals across the nation and beyond.

The impact for clinical care is also immense. Research offers increased monitoring and more intensive follow-up as compared to routine clinical care. Use of measurement-based approaches, and family and patient engagement to co-design care, will provide templates for future models of care and best practice. Furthermore, this initiative will address the huge gaps in physical care that drive morbidity and premature mortality in this population. We anticipate that these efforts will open up the potential for system level change to ensure individuals are treated from all health-related (i.e. physical and mental) perspectives, also bridging medical and mental health care for individuals with SSDs.

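### The ICES contrast labelled CAMH services rests on consenting study participants, some already in CAMH care and followed from study entry, so it does not isolate a service effect

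*Protocol*

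**What the plan says.** Section 3.9.1 lists three groups for the administrative-data comparison. The first is described as "Participants that are part of the cohort at CAMH (accessing specialized mental health services at CAMH", and entry depends on a second consent: "Participants who consent to have their data linked with administrative health data will be eligible to have both historical and future services use linked". The other two are people with SSD identified in ICES data, one group using community specialized services and one using none. They are "restricted to people who have not received regular outpatient services at CAMH".

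Section 3.9.2 matches the linked participants 1:1:1 to these two groups on a propensity score. It names the exposures thus: "This will enable the comparison of three exposures (CAMH services, community services, eligible but no service". On what the matching yields, it states: "Estimated treatment effects can then be obtained by directly comparing outcomes between matched groups". It adds a general caution that matching cannot deal with unmeasured confounding.

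Section 3.9.4 counts mental health hospitalizations after cohort entry as the primary outcome, and section 3.9.6 adds a cost comparison. Section 3.9.5 lists among the covariates "regular metabolic monitoring, regular CBC monitoring for clozapine use", and explains in a bracket that the CBC item is there because clozapine claims are not reliably reported.

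Recruitment and Sampling in section 5.0 states that both new and existing CAMH patients are enrolled and that assessment results go to the clinical team. Section 3.2 adds former research participants as a recruitment source.

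**The concern.** A difference between the first group and the comparators would be read as an effect of CAMH services on admissions and cost. Three other things differ along with the service.

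- **Selection.** Everyone in the CAMH arm agreed to join a three-year study and to have records linked. Nobody in the comparators was asked.
- **Study participation.** Section 8.0 says: "Research offers increased monitoring and more intensive follow-up as compared to routine clinical care". Whatever the study adds, it adds to one arm only. It coincides with arm membership, so no covariate can balance it.
- **Prior care.** Existing patients enter at study entry, not at the start of CAMH care. Section 5.0 describes "metabolic monitoring being implemented across these clinical services", so for these patients the metabolic monitoring covariate may record care that CAMH has already delivered. Matching on it would then adjust away part of the effect of interest.

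The propensity score is built to balance patient characteristics at entry. It does not address the second and third items, and it addresses the first only as far as willingness to take part is captured by the listed covariates.

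**Working it through.** The protocol gives no sample size, event rate or effect size for the ICES analysis, so there is no figure of its own to reproduce. The main check is a reading of sections against each other. The two calculations only show how such biases behave.

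**1. Who is in the CAMH arm, and who is in no arm.** Section 5.0 aims for 1000 participants over two years and reports more than 4000 outpatients seen in one year. 1000/4000 = 25%, so the arm is at most about a quarter of one year's outpatient volume, before the linkage consent. This is not a participation rate: inpatients are also recruited and the periods differ. CAMH patients outside the study are not in group 1, and those with regular CAMH outpatient care are excluded from groups 2 and 3. Nothing in the design therefore separates being a CAMH patient from being a participant.

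**2. Time zero and covariates.** Section 3.9.4 starts the outcome at cohort entry. Section 3.9.2 speaks of baseline covariates, but for an existing patient baseline falls after CAMH care began. Section 3.9.5 sets no window ending earlier. Section 3.6 describes metabolic monitoring as part of routine clinical care.

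**3. Illustration of a participation effect (all inputs assumed).** True CAMH rate ratio 1.0; participation rate ratio v; n per arm; 3 years; annual admission rate r = 0.3 to 0.6; negative binomial shape k = 0.5 to 1.0; two-sided 5% Wald test; pairing ignored.

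- m = 3r; Var(log RR) = [(1/(m·v) + 1/k) + (1/m + 1/k)]/n; z = |ln v|/SE; P(reject) = Φ(z − 1.96) + Φ(−z − 1.96).
- Lowest corner, n = 1000, v = 0.85, r = 0.3, k = 0.5: m = 0.9; Var = (1.307 + 2 + 1.111 + 2)/1000 = 0.00642; SE = 0.0801; z = 0.1625/0.0801 = 2.03; P = 0.53.
- Highest corner, r = 0.6, k = 1.0: m = 1.8; Var = (0.654 + 1 + 0.556 + 1)/1000 = 0.00321; SE = 0.0566; z = 2.87; P = 0.82.

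| v | n = 1000 | n = 750 |
|---|---|---|
| 0.90 | 0.26–0.46 | 0.21–0.37 |
| 0.85 | 0.53–0.82 | 0.42–0.70 |
| 0.80 | 0.79–0.97 | 0.67–0.92 |

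The 750 column allows for incomplete linkage consent (assumed).

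**4. Illustration of over-adjustment (all inputs assumed).** Let CAMH raise regular monitoring from p0 to p1, let monitoring have outcome rate ratio g, and let the direct CAMH rate ratio be d = 0.9. Then total RR = d(1 − p1 + p1·g)/(1 − p0 + p0·g). Matching on monitoring leaves d, so the share of the log effect removed is 1 − ln d/ln(total).

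- p1 = 0.8, p0 = 0.3, g = 0.8: total = 0.9 × 0.84/0.94 = 0.804; share = 1 − 0.1054/0.2178 = 0.52.
- Over p1/p0 of 0.8/0.3, 0.8/0.5 and 0.6/0.4 and g of 0.7 to 0.9, the share is 0.17 to 0.63 if all participants are existing patients.
- In the first case with half existing: log RR = 0.5(−0.1054) + 0.5(−0.2178) = −0.1616; share = 1 − 0.1616/0.2178 = 0.26. With all new patients and covariates measured before CAMH care, it is 0.

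A participation rate ratio below 1 makes CAMH look better. Over-adjustment of this kind makes it look less effective. The two can oppose each other.

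**The case against.** The strongest reply is that the protocol discloses the arm for what it is. Section 3.9.1 calls it the cohort, and section 3.9.2 concedes unmeasured confounding, which covers willingness to volunteer. Eligibility is broad, including inpatients and people who enter through a substitute decision-maker, so selection may be mild. Core assessments largely mirror routine care and section 4.0 reuses data already collected, so the study's added monitoring may be small. Its effect on admissions is not shown. A covariate window is commonly left to an analysis plan. The comparison also serves none of Objectives 1 to 3.

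Much of this limits the size of the problem. It does not remove it. The general caution does not cover a study contact given to one arm, or entry after the service began. The exposure label, the treatment-effect language and the outcome origin are set in the protocol itself.

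A reader might infer four stronger points that the documents do not support.

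- **Matching keeps only monitored people in the no-service group.** Matching is on a single score, not on each covariate, and section 3.9.3 draws on province-wide laboratory data, so monitoring can occur and be recorded outside CAMH.
- **CBC monitoring should be dropped as well.** Section 3.9.5 uses it as the stand-in for clozapine use. Dropping it would remove the only listed marker of that treatment.
- **Over-adjustment affects everyone.** It needs an existing patient, a window running past the start of CAMH care, and an effect of monitoring on the outcome. The last is less plausible for mental health admissions than for the medical outcomes.
- **The bias favours CAMH.** The direction is not known.

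**Conclusion.** The concern holds in limited form. As fixed in sections 3.9.1 to 3.9.5, the analysis compares linked CAMH cohort participants with administrative-data controls. It cannot attribute a difference to CAMH services alone, because service, volunteering, study contact and earlier care are not separated and no group of CAMH non-participants exists to separate them.

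The size cannot be estimated from the documents: the share of existing patients, the linkage consent rate, the admission rate and any participation effect are all unstated. The rejection rates of 53% to 82% (rate ratio 0.85) and 79% to 97% (0.80), and the 17% to 63% of log effect removed, rest wholly on assumed inputs. They show only that modest biases would matter at this sample size.

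The point should be dealt with before the ICES analysis. It does not touch the trajectory objectives.

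**What to change.** 1. Label group 1 CAMH cohort participants in sections 3.9.1 and 3.9.2, and do not attribute its differences to CAMH services alone.
2. Add a group of CAMH patients with SSD outside the study. The exclusion rule in section 3.9.1 already requires regular CAMH outpatients to be identified. Report participants against CAMH non-participants, as the check on volunteer and study effects, and CAMH non-participants against the two comparators, as the contrast closer to a service effect.
3. Measure regular metabolic monitoring before first CAMH contact, using the ICES lookback in section 4.0, or leave it out of the propensity score for existing patients. Report a new-patient analysis with the index date at the start of CAMH care, and state the corresponding index date and window for the comparators.
4. Keep CBC monitoring as the marker of clozapine use, measured before the index date.

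**Cost.** An amendment to sections 3.9.1 to 3.9.5 and added analyst time at ICES. CAMH attendance may be misclassified for non-participants: section 3.9.3 does not say which data holding identifies it, a gap that the present exclusion rule shares. The new-patient analysis will be less precise. Item 1 costs only the wording and can be done regardless of the rest.

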**3.9.3 Data sources**

Linkages will occur across the following ICES data holdings: the Registered Persons Database (RPDB) which is a central population registry that contains basic demographic data on all people insured by OHIP; the Ontario Mental Health Reporting System (OMHRS) which contains data on all inpatient hospitalizations to adult mental health beds; the Canadian Institute for Health Information Discharge Abstract Database (CIHI-DAD) containing data on all acute care hospitalization and mental health hospitalizations before 2005; the National Ambulatory Care Reporting System (NACRS) which contains data on emergency department visits; outpatient physician billings from OHIP; the Ontario Drug Benefit (ODB) claims which contains data on medications dispensed through publicly funded program for eligible people; the Ontario Laboratories Information System (OLIS) containing laboratory data across the province, the Ontario Registrar General (ORG) for information on deaths; and the Ontario Marginalization Index (ON-Marg) which is an area-level deprivation index based on census data

**3.9.4 Outcomes**

The primary outcome will be the number of mental health hospitalization following the cohort entry period. Secondary outcomes will include the number of medical hospitalizations, days spent in hospital (both in mental health and medical beds), ED visits, suicide and self-harm attempts and mortality.

**3.9.5 Covariates**

Covariates that will be accounted for will include: age, sex, immigration status, neighbourhood-level marginalization (consider neighbourhood as well), diagnosis, history of substance use related health care contacts, enrollment with a family physician, ODB eligibility, long-acting antipsychotic medication claims, claims for medications for specific comorbid health issues (i.e., metformin, statins), regular metabolic monitoring, regular CBC monitoring for clozapine use (as at the present time clozapine claims are not regularly reported).

**3.9.6 Data Analysis**

Descriptive statistics will be used to characterize outcomes and covariates. Balance between groups will be assessed. Based on the type and distribution of the outcome data appropriate regression models will be fit accounting for the matched nature of these data.

*Cost analysis*

A standard ICES costing methodology and algorithm [(Wodchis et al., 2013, 2016)](https://www.zotero.org/google-docs/?IQrY21) will be used to estimate all health care costs incurred within the publicly funded provincial health care system. Costs will be identified for all hospitalizations (psychiatric and non-psychiatric), ED visits, physician visits (across all specialties), diagnostic tests, prescription drugs of those covered under via ODB, as well as other publicly funded services. Costs will be compared between comparison groups as well as between trajectories identified within the cohort.

**3.10 EMR-based Natural Language Processing (NLP) and Machine Learning (ML) for the characterization of longitudinal clinical course and outcomes**

Data will be extracted from the CAMH EMR and the Enterprise Data Warehouse for EMR-based retrospective characterization of the longitudinal clinical course and outcomes for study participants. Structured data elements that overlap with measures utilized for prospective cohort characterization (described above) will include sociodemographic data, administrative data related to treatment encounters, as well as clinical data (including diagnoses, medical problem lists, prescribed medications, laboratory data, anthropometric measures, and structured assessments of psychopathology (e.g., BPRS, CGI, BCATS) and functioning (e.g., WHO-DAS, PSP/SOFAS). In addition, free text clinical notes pertaining to consenting study participants will be also extracted.

To evaluate various approaches for preprocessing and extracting features from the free text clinical notes of study participants, we will first analyze any available structured data (i.e., demographics, visit frequency, outcome measures) and free text clinical notes pertaining to patients with schizophrenia spectrum disorders at CAMH (Phase 1). This will be followed by our second analyses (Phase 2) that comprise the analytic approaches developed in Phase 1 applied and validated with the free text clinical notes for consenting participants that are enrolled in this study. For Phase 1, however, because these notes are analyzed without patient consent, we will use REB-approved protocols developed in other studies (e.g., 157-2018, 156-2020), which ensure that the study team only access numerical features derived from the notes. Accessing and analyzing these numerical features, instead of the notes in their raw form, reduces privacy risks of accessing sensitive or identifiable information contained within the notes.

Before any clinical notes from the CAMH medical records are accessed by the study team (i.e., for study participants and CAMH patients), they will be de-identified. [name], Integration Manager with IMG Clinical Applications at CAMH, will extract a copy of the clinical notes from I-CARE and securely transfer this copy of the raw data to the enterprise data warehouse on secure clinical servers, where their access is restricted to IMG Clinical Applications personnel authorized to support this study. At this point, clinical applications will configure CRATE, an anonymization software [(Cardinal, 2017)](https://www.zotero.org/google-docs/?jYkokH), to remove direct identifiers from the clinical notes. The software’s configuration will be refined to achieve the highest possible recall, with an estimated 89-100% of the direct identifiers being removed from the clinical notes. These direct identifiers include names, dates of birth, medical record numbers (MRNs), address components, telephone numbers, email addresses, aliases and third-party information (i.e., names of family members or other non-professional contacts). IMG accomplishes this configuration by securely populating the CRATE data dictionary with direct identifiers (such as, but not limited to, names, phone numbers, MRNs) associated with existing CAMH clients from I-CARE, with a large database of names, surnames, and addresses (independent of those added from I-CARE), and regular expressions, which are characters that represent patterns of text (e.g., phone number patterns, medical number patterns), similar to wildcards. Once the data dictionary is generated, CRATE works by comparing words in the clinical notes against those in the data dictionary. If there is a match, it removes those words from the clinical notes. Once CRATE is configured, clinical applications will perform unit tests, which involve passing texts with only potential identifiers in them (such as names and sets of dummy phone numbers, MRNs, e-mail addresses) through CRATE. If CRATE purges 100% of the document (i.e., no text remains), it will be deemed successful enough to be used on the clinical notes. At this point, CRATE will be used to de-identify the clinical notes.

For Phase 1, involving analyses on retrospective clinical documentation pertaining to CAMH patients with schizophrenia spectrum disorders, IMG applications personnel will implement NLP methods (similar to those described below for Phase 2 analyses) to convert the clinical notes into features, which will then be shared with the study team. This process ensures that the study team do not access raw clinical notes for retrospective patients who have not formally provided their consent to participate in the study. For these patients, only IMG personnel will have access to the clinical notes in their raw form, no one (not even IMG personnel) will see or review individual notes, and what is extracted and accessed by the research team will not be directly or indirectly identifiable. The study team will also access the following structured data pertaining to the CAMH clients represented in the clinical notes: sociodemographic information from the Health Equity Form, CAMH visit frequency, type, and location, diagnoses, medical problem lists, prescribed medications, laboratory data, anthropometric measures, as well as any available outcomes measured with the WHO-DAS, BPRS, CGI, PSP, B-CATS, AIMS, BARS, and SARS. In Phase 1, we aim to develop and refine methods for extracting meaningful patterns ad trends from the clinical note features, which involves evaluating various text preprocessing and modelling strategies. The structured data will be used as part of this evaluation to validate patterns and trends identified within the notes, based on the various preprocessing and modelling strategies being investigated. We will also use the structured data to gauge the sociodemographic and clinical representativeness of the Phase 1 sample.

For Phase 2 analyses involving consenting study participants, once direct identifiers have been removed, the raw clinical notes for study participants will be shared with the study team, who will implement NLP methods in the R programming language to automatically convert the clinical notes into features. Converting the notes into features disrupts the order of the words and their context, or it reduces the text to numerical data representing various characteristics (e.g., polarity, semantics). For instance, the study team will generate a document-term matrix, containing words from the clinical notes as columns and their frequencies in each note as rows. This matrix will be utilized for topic modeling, an unsupervised ML algorithm to discover themes and generate temporal patterns and trends to investigate trajectories of outcomes and clinical phenomena in the study population. These temporal patterns will be linked with structured data for that participant available both from the EMR (including their age, sex, ethnicity, socioeconomic status, clinical and outcome measures where available (e.g., BPRS, CGI, WHO-DAS, PSP, B-CATS, AIMS, BARS, SARS), medication prescriptions, treatment encounters), as well as with the prospectively collected outcome, clinical, physical health, socioenvironmental, and biological data as part of this study.

We will store all study data (including data from the CAMH EMR, such as the structured data and de-identified clinical notes) on the CAMH Neuroinformatics platform for the entire duration of the study, and its availability will be restricted to the study team. The study team will use the remote server to access and analyze the data. If the study team wishes to use the data for purposes that were not outlined in the current version of the protocol, or if other individuals wish to access the data, the research team will submit an amendment or a new ethics application to the CAMH REB. The data will remain on the server, and it will never be downloaded on any computers or devices. The CAMH Neuroinformatics platform automatically tracks the activity of all its users; it keeps a record of individuals who log into the platform, the software they use, the data they access, and what they do with the data. This will allow for audits of who has accessed the document-term matrices and for what purpose these data were accessed.

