The Health, Social and Justice Service Use Inventory (HSJSU) was developed to assess service use and estimate services costs as part of the large multi-site At Home/Chez Soi RCT of a Housing First intervention [(Goering et al., 2011)](https://www.zotero.org/google-docs/?YGRSvY). This tool was initially used to evaluate service use in a sample of Canadians with serious mental illness experiencing homelessness and developed based on a number of prior tools and measures with varying psychometric properties [(Guerriere et al., 2006; Kashner et al., 2009; Sirey et al., 2005)](https://www.zotero.org/google-docs/?HJgPWD). Through the proposed linkage with administrative health data that will be undertaken as part of this study validation of this Canadian designed measure will be undertaken.

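### The cost comparison between service groups claims all public health care costs, but the listed data sources do not cover non-physician programme care, so served groups may look too cheap against no service

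*Protocol*

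**What the plan says.** Section 3.9.6 applies a standard ICES costing method to "estimate all health care costs incurred within the publicly funded provincial health care system". It then itemises: "Costs will be identified for all hospitalizations (psychiatric and non-psychiatric), ED visits, physician visits (across all specialties), diagnostic tests, prescription drugs", the drugs being those covered by ODB. It closes the list with "as well as other publicly funded services", without naming a service or a data source. The contrast is stated in the same paragraph: "Costs will be compared between comparison groups as well as between trajectories identified within the cohort".

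Section 3.9.1 defines three groups: cohort members using specialised mental health services at CAMH; people using such services in the community, "including ACT, ICM and case management services but not at CAMH"; and Toronto residents with an SSD who are not currently receiving them.

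Section 3.9.3 lists nine holdings for linkage: RPDB, OMHRS, CIHI-DAD, NACRS, OHIP billings, ODB, OLIS, ORG and ON-Marg. The only entry described as outpatient care is "outpatient physician billings from OHIP".

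Section 3.8 includes the HSJSU, which "was developed to assess service use and estimate services costs". Appendix 1 schedules it at months 0, 12, 24 and 36, for study participants only.

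**The concern.** The protocol itself fixes the cost scope, the contrast and the data sources, and the three do not fit together. The cost component without a visible source is also part of the exposure. A person in the no-service group has close to none of it, at least at entry; people in the other two groups have some by definition. The omission is therefore differential. An admission averted by a team would be credited to the served group, while the non-physician staff time behind it would not be charged.

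Propensity matching (3.9.2) and the covariates in 3.9.5 cannot repair this, because what is missing is part of the outcome. At stake is an apparent saving with CAMH or community care that arises only from what was counted.

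**Working it through.** The plan states no cost figure, effect size or power for this comparison, so there is nothing to reproduce. The check sets the sections side by side and then works out the form of the bias.

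**Step 1. Cost components (3.9.6) against holdings (3.9.3).**
- Hospital stays: OMHRS and CIHI-DAD.
- ED visits: NACRS.
- Physician visits: OHIP billings.
- Tests: OLIS (laboratory data).
- Drugs: ODB.
- Other publicly funded services: no holding named.
- RPDB, ORG and ON-Marg hold demographics, deaths and area deprivation, and carry no cost item.

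Holdings described as carrying non-physician outpatient care, ACT, ICM or case management: 0 of 9.

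**Step 2. What this leaves out in each group (3.9.1).**
- CAMH: non-physician outpatient care. Section 3.1 admits inpatients, and their stays and billed physician visits are covered.
- Community: ACT, ICM and case management, apart from any physician visits billed to OHIP.
- No service: close to nothing at entry.

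**Step 3. Form of the bias.** Let U1, U2 and U3 be the uncaptured programme cost per person-year with CAMH, community and no service. For any two groups a and b:

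counted difference (a − b) = full difference − (Ua − Ub).

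- CAMH minus none: error −(U1 − U3), about −U1 if U3 is near zero.
- Community minus none: error −(U2 − U3), about −U2 on the same condition.
- CAMH minus community: error −(U1 − U2). The documents do not give its sign.

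**Step 4. Relative size, on assumptions.** Let f be the programme share of a group's true public cost and s the share of programme cost already captured through billings and inpatient days. The group's cost is understated by f × (1 − s). Neither f nor s is in the documents.

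| f | s = 0% | s = 25% | s = 50% |
|---|---|---|---|
| 10% | 10% | 7.5% | 5% |
| 25% | 25% | 18.75% | 12.5% |
| 40% | 40% | 30% | 20% |

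If true total cost equalled that of the no-service group, and that group had no uncaptured cost, the apparent cost ratio would be 1 − f(1 − s): from 1 − 0.40 = 0.60 to 1 − 0.05 = 0.95.

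**Step 5. Break-even, on assumed figures.** Suppose counted cost is 6,000 per person-year lower with CAMH care than with no service, and U3 is zero. With U1 = 2,000 the full difference is −6,000 + 2,000 = −4,000. With U1 = 15,000 it is −6,000 + 15,000 = +9,000. The sign changes at U1 = 6,000. The amounts are invented; the point is that the threshold equals the counted saving and can be reported without knowing U1.

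**The case against.** The strongest reply is that section 3.9.6 relies on a cited costing method and expressly includes other public services, while section 3.9.3 lists holdings for linkage without saying that costing stops there. The method may cover more than the list shows. This stands in part: the documents support saying that no source is named, not that programme cost will certainly go uncounted. It does not remove the inconsistency. Either a source exists and belongs in 3.9.3, or the claim to all costs must go.

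A related reply is that no listed holding is described as identifying ACT, ICM or case-management receipt either. If the list is closed, the community group cannot be formed as defined; if it is open, whatever identifies these services may also cost them. That is fair, and it is a further reason to name the source.

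Four stronger readings are tempting and are not supported:
- A reader might infer that served groups look cheaper by their whole programme cost. OHIP-billed visits and inpatient days are counted, so only the uncaptured part is lost.
- A reader might infer a known direction for every contrast. It is known only against no service. Even there, people not currently served may enter services later, which would shrink the gap.
- A reader might tie the hope for more cost-effective services in section 8.0 to this contrast. That passage concerns predicting trajectories and developing interventions. Section 3.9.6 plans no cost-effectiveness analysis, and 3.9.4 does not list cost as a primary or secondary outcome.
- A reader might infer that the HSJSU is excluded from the trajectory comparison. Section 3.9.6 is silent on it, and section 4.0 sends participants' study data to ICES.

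**Conclusion.** The point holds in limited form. Section 3.9.6 promises all publicly funded costs across groups defined by a type of service, and no holding in 3.9.3 is described as recording the non-physician part of that service. If costs are built from the listed holdings, the CAMH and community groups are understated by their uncaptured programme cost, and both are favoured over no service. Between CAMH and community the direction is unknown.

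The size cannot be derived from the documents. The 5% to 40% range rests wholly on the assumed f and s, and the ratios of 0.60 to 0.95 also assume equal true totals and no uncaptured cost in the no-service group. The conclusion further assumes that the cited costing method adds no source beyond those listed, which cannot be checked here.

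This is an ancillary analysis and the main objectives are unaffected. The correction is still worth making, because the bias could by itself produce an apparent saving.

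**What to change.** In sections 3.9.3 and 3.9.6, do one of two things.

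1. Name a source that supplies programme costs for all three groups, and keep the claim to full cost.
2. For the between-group comparison, limit the claim to the components that have a listed source: hospital, ED, physician, diagnostic and laboratory tests, and ODB drugs. State that uncaptured programme cost biases the contrast in favour of the served groups over no service. Report the uncaptured programme cost per person-year at which each difference becomes zero. Draw no conclusion on total cost.

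For trajectories within the cohort, HSJSU and CAMH encounter data may be added as a supplementary analysis. It should cover only participants who have those data, since ICES linkage is by consent (3.9) and 25% attrition is assumed (5.0). It should be limited to services not already costed at ICES, to avoid double counting; section 3.8 also shows that validation of the HSJSU against administrative data is still to come.

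The second option costs a change of wording and a simple threshold calculation, and the supplementary analysis uses data already scheduled. The price is a narrower cost claim. The first option's cost depends on whether such a source is available, which the documents do not show.
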